## 12. ASSESSMENT OF SAFETY

### 12.1. Safety measurements

Safety measurements during the study, as indicated in Figure (8.2.2) 1– Investigation schedule, are:

- Recording of adverse events including hypoglycaemia at each visit.
- Reviewing of cardiovascular events by the Adjudication Committee.
- Assessing the aetiology of oedema at inclusion and during the study (see appendix 11).
- Centralised biochemistry focusing on ALAT, lactic acid and haematology with haemoglobin, haematocrit follow-up.
- NT-proBNP follow-up.
- Body weight, heart rate, blood pressure, ECG and echocardiography.

### 12.2. Methods and measurement times

- **Hypoglycaemic episodes:** each patient likely to be included will receive training on diabetes education by the investigator. He will be informed about trigger factors of hypoglycaemia and symptoms suggestive of hypoglycaemia and will be instructed about the procedure to follow in case of any symptom suggestive of hypoglycaemia: then he will be instructed to take immediately afterwards sugar, food or fluid containing sugar (as described in the patient's diary card) and then to report the episode in his diary card. The patient will return his diary at each visit. At the study visit, the investigator will check for occurrence of hypoglycaemic episodes by patient questioning and examination of patient's diary card. For management and specific reporting of episodes suggestive of hypoglycaemia, see appendix 8.
- **Oedemas:** the investigator will carefully monitor occurrence of pedal oedema at each study visit. If oedemas develop see appendix 11.
- **Heart failure:** In case of suspicion of heart failure, the investigator will refer the patient to a cardiologist (see appendix 10).
- **Centralised biochemistry and haematology assessments**  
All the laboratory parameters will be assessed by a central laboratory during the study. The sampling will be performed locally within the 7 days before the planned study visit in order to get the results available at the visit. The patients will have to be in fasting conditions and have stopped taking their OAD (study treatment and sulfonylurea) since at least 8 hours before sampling. Sampling and shipment materials will be provided by the central laboratory. The methods for sampling, handling and analysis will be fully detailed in the instruction manual provided by the central laboratory. The normal laboratory values will be also provided prior to the start of the study and updated if necessary during

the study. They will be present on every laboratory report. The investigator will be responsible for the clinical assessment of the biological results.

**The following safety laboratory assessments will be performed:**

- Standard haematology: red blood cell count, red blood cell indexes, white blood cell count, differential white blood cell count, blood smears, platelet count. They will be assessed at each visit and in case of premature discontinuation.
- Biochemistry
  - o Total proteins, creatinine, albumin, sodium, potassium, chlorides calcium, total bilirubin, alkaline phosphatase. They will be assessed at W0, W28 and W52 and in case of premature discontinuation.
  - o Lactic acid and uric acid will be assessed at W0, W52 and in case of premature discontinuation.
- NT-proBNP will be assessed centrally at W0, W28, W52, in case of premature discontinuation and in case of oedema (to evaluate an underlying heart failure).

**Liver enzymes** (ALAT, ASAT,  $\gamma$ -GT) will be assessed at W0, W4, W8, W16, W28, W40, W52 and in case of premature discontinuation.

- **If ALAT level is > 2.5 times the upper normal limit prior to inclusion, the patient should not be included.**
- **If ALAT level is > 3 times the upper normal limit after inclusion,** a re-test should be performed within 7 days. If the value remains 3 times the normal upper limit, the study treatment will be stopped and the patient withdrawn.
- **In case of unexplained symptoms suggestive of hepatic disease** (nausea, vomiting, abdominal pain, fatigue, loss of appetite, jaundice, dark urines), complete liver function tests should be performed. Until the results are obtained, the decision to maintain study treatment will relay on clinical judgement. In case of jaundice, the study treatment will be discontinued.

**Haemoglobin and haematocrit will be assessed** at every visit and in case of premature discontinuation.

- **If, at inclusion, haemoglobin level is < 12g/dL in men and < 11g/dL in women, the patient should not be included.**
- **If, after inclusion, clinically significant anaemia** is detected, see appendix 12.

The results (with the clinical assessment of the investigator) will be included in the CRF and one copy kept in the patient file. The investigator will report in the adverse event section of the CRF the abnormal biological parameters **only** if considered as clinically significant and not already reported/considered as pre-existing conditions without aggravation.

- **Body weight, heart rate, blood pressure, ECG and echocardiography:**
  - o The body weight will be measured at each study visit particularly in case of oedema and congestive heart failure, in the same conditions (same scales, patient lightly dressed, without shoes). The patient will be encouraged to control his body weight all along the study and to report any unusual weight gain, particularly if the onset is acute and the weight increases rapidly (around 2 kg within one week).

- Heart rate and blood pressure will be measured at each visit in the same conditions: sitting position after a 10 minutes rest. For a given patient, blood pressure will be measured on the same arm during the whole study.
- ECG 12-lead as well as echocardiography (with central reading) will be performed between ASSE and W0 (to be available at inclusion visit), at W52 and in case of suspicion of heart failure.

### 12.3. Adverse events

At each visit, adverse events will be recorded in the CRF (see section 12.3.1.). Assessment will be performed by questioning the patient and by physical examination including vital signs (sitting systolic and diastolic blood pressure, heart rate).

All adverse events must be followed up, fully and precisely documented to enable assessment of the safety of the study drug.

#### 12.3.1. Responsibilities of investigator

##### 12.3.1.1. Recording of adverse events in the case report form

###### 12.3.1.1.1. Events to be recorded

An adverse event is defined as any untoward medical occurrence in a subject participating in a clinical study, whether or not there is a causal relationship with the study drug and/or experimental procedures, occurring or detected from the participant's signature of information and consent form, whatever the period of the study (periods without administration of the study drug are also concerned).

The investigator must therefore document as an adverse event:

- any unfavourable and unintended sign, including an abnormal finding from an additional examination (laboratory tests, X-rays, ECG, ...) deemed clinically relevant by the investigator,
- any symptom (including symptoms suggestive of hypoglycaemia) or intercurrent disease,
- any worsening during the study of a symptom or a disease already present when the participant entered the study (increase in frequency and/or intensity), and which:
  - is detected during a study visit or at an additional examination,
  - occurred since the previous study visit and is notified by the participant,
  - is documented by the participant in his/her diary card, when the investigator considers it clinically relevant.

An adverse event must be **notified immediately** when it is:

- a **serious adverse event**, i.e. an event which, whatever the dose of the study drug administered:
  - **results in the death of the participant,**
  - **is life-threatening:**

*Note:* the term “life-threatening” refers to an event in which the patient was at risk of death at the time of the event; it does not refer to an event which hypothetically might have caused death if it were more severe,

- **is medically important:**

*Note:* any event that may not be immediately life-threatening or result in death or hospitalisation, but may jeopardise the participant or may require intervention to prevent one of these outcomes (for example: oedema or allergic bronchospasm that required intensive treatment at home, blood dyscrasia, convulsions that do not result in hospitalisation, or development of drug dependence or drug abuse, heart failure, myocardial infarction...). The investigator should exercise his/her scientific and medical judgement to decide whether or not such an event requires expedited reporting to sponsor

- **requires inpatient hospitalisation or prolongation of existing hospitalisation,**

- **results in persistent or significant disability / incapacity:**

*Note:* any event that seriously disrupts the ability of the participant to lead a normal life, in other words leads to a persistent or permanent significant change, deterioration, injury or perturbation of the participant's body functions or structure, physical activity and/or quality of life,

- **an overdose of the study drug:**

*Note:* any accidental or deliberate overdose with the study drug in the participant or a person in his/her family (e.g. child) must be notified, whether or not it has medical consequences (serious or non-serious adverse event, or absence of signs and symptoms).

Sofar as possible, a blood sample should be collected for possible assay of the study drug taken. The sampling technique and the method of storage are described in appendix 9.

- **pregnancy**

Should anyone of the study participant become pregnant, the investigator must:

- stop the participant's treatment
- report the pregnancy to one of the persons named in section 12.3.1.3
- contribute to the follow-up of this pregnancy and provide the sponsor with the relevant information.

- **severe hypoglycaemia** (see appendix 8)

#### 12.3.1.1.2. Recording methods

Adverse events must be documented on an "Adverse event" form ("Initial information" page and if necessary "Additional information" pages) according to the general instructions for completion appended in the CRF

Some sections of the page must always be completed, whether or not the event requires immediate notification. Further sections must be completed only when the event requires immediate notification.

In the case of disease progressing by episodes (chronic disease):

- if the disease is known when the participant enters the study, only worsening (increased frequency and/or intensity of the episodes/attacks) will be documented as an adverse event,
- if the disease is detected during the study and if repeated episodes enable diagnosis of a chronic disease, the episodes will be grouped on the same page "Adverse event – Initial information" which will clearly describe the diagnosis.

For the following adverse events, additional information will be requested and specific procedure should be followed:

- **Hypoglycaemia:** the episodes of hypoglycaemia will be recorded on the « Suspected hypoglycaemia form ». See specific procedure Appendix 8.
- **Oedemas:** See specific procedure Appendix 11.
- **Heart failure:** See specific procedure Appendix 10.
- **Anaemia:** See specific procedure Appendix 12.

#### 12.3.1.2. Follow-up of adverse events

The investigator must ensure that follow-up of the participant is appropriate to the nature of the event, and that it continues until resolution. He/She must immediately inform the sponsor of any secondary worsening.

Any change in terms of diagnosis, intensity, seriousness, measures taken, causality or outcome regarding an adverse event already reported must be written up in a new complete evaluation of the event documented on the "Adverse event - Additional information" page.

If the adverse event has not resolved at the participant's final visit in the study, the participant must be followed up suitably and any information on the outcome of the event will be noted on an "Adverse event – Additional information" page.

If the follow-up of the participant is not done by the investigator him/herself (hospitalisation, followed by a specialist or the participant's general practitioner, ...), the investigator will do everything to establish/maintain contact with the person/department in charge of follow-up of

the participant, so as to have additional information and report it on an "Adverse event - Additional information" page.

### 12.3.1.3. Procedure for an event requiring immediate notification

In the case of an event requiring immediate notification that occurs:

- during the study, or,
- during the 30 calendar days after the participant's final study visit, regardless of the supposed role of the research (study drug or experimental procedures required by the technical protocol) or,
- beyond these 30 days, irrespective of the time of onset after the end of the study, if the event is likely to be due to the research,

the investigator must:

- **note** in the participant's medical file the date on which he/she learned of the event (at a follow-up visit or a telephone contact with the participant or a third person, ...),
- **immediately inform** by telephone or fax:

| COUNTRY       | STRUCTURE | PERSON(S) TO BE CONTACTED | PHONE NUMBER       | FAX NUMBER         |
|---------------|-----------|---------------------------|--------------------|--------------------|
| FRANCE        | CRO       | [name]                   | [contact]  | [contact]  |
| ARGENTINA     | CRO       |                           |                    |                    |
| GERMANY       | CRO       |                           |                    |                    |
| INDIA         | CRO       |                           |                    |                    |
| SOUTH AFRICA  | CRO       |                           |                    |                    |
| ALL COUNTRIES | I.R.I.S.  | [name]               | [name] | [name] |
| ALL COUNTRIES | I.R.I.S.  | Help Desk                 | [name] |                    |

- complete an "Adverse event – Initial information" page of the CRF according to the general instructions appended in the CRF, and send it by fax to the persons responsible designated above, **immediately** after of being informed of this event, without waiting for the results of the clinical outcome or of additional investigations. As soon as the "Adverse event – Initial information" form is completed, and according to DPP solution, an alert e-mail will warn monitors, medical reviewers and I.R.I.S.
- provide the persons designated above, as they become available, with anonymised copies of the documents which provide additional useful information, such as hospital admission reports, reports of further consultations, laboratory test reports, reports of other examinations leading to diagnosis (where possible, the results from pre-treatment assessments should be appended for comparison with the results obtained under treatment), or the autopsy report, if autopsy is performed,
- fulfil his/her regulatory obligations to the Regulatory Authorities and/or to the Ethics Committee, in accordance with local regulations.

If an adverse event initially non-serious worsens and becomes serious, this must be reported **immediately** to the persons designated above and documented on an "Adverse event - Additional information" page. The investigator should fax **immediately** together the "Initial information" and "Additional information" pages to these persons.

If a female participant in the study becomes pregnant, the investigator must:

- stop the participant's treatment,
- complete an "Adverse event – Initial information" page of the CRF and fax it **immediately** to the person designated above for the country,
- complete a pregnancy follow-up report form (1st page) send by I.R.I.S.,
- contribute to the follow-up of this pregnancy and provide the sponsor with information concerning this follow-up (notably using the 2nd page of the pregnancy follow-up report form).

#### **12.3.1.4. Evaluation of causality**

It is important that the investigator gives his/her opinion regarding the cause-effect relationship between an adverse event and the study drug, for the following reason: certain adverse events that occur during clinical investigations can be sufficiently significant to lead to changes in the drug development programme (for example: change in dose, study population or in the information given to participants that may lead to the preparation of new information and consent forms). This is particularly true for events suspected to be related to the study drug (adverse drug reaction) and which, in their most severe forms, are life-threatening.

In the case of a drug interaction study, the causality will be evaluated regarding the study drug and not the associated treatment(s).

#### **12.3.2. Responsibilities of sponsor**

Independently of the regulatory obligations of the investigator, the sponsor must report the pharmacovigilance data to the appropriate Authorities and to all the investigators involved, according to the requirements stated in ICH Good Clinical Practice guidelines and local regulations.

#### **12.3.3. Responsibilities of Adjudication Committee**

Refer to section 16.4.2

### **13. OTHER ASSESSMENTS NOT SPECIFICALLY RELATED TO EFFICACY OR SAFETY**

#### **13.1. Economic balance**

For the purpose of a further pharmacoeconomic evaluation comparing the economic outcomes of the two treatments, the investigator will report on a specific page of the CRF in case of adverse events the additional information:

- duration of the illness, GP visit, specialist visit or paramedical visit in addition to the study visits,
- in case of hospitalisation: duration of hospitalisation, type of service (emergency, intensive care unit...) and prescription at discharge,
- exam and procedures other than those required by the protocol (biological, ophthalmological, ECG...),
- transportation costs to access to health care services, if any,
- any dose modification of previous treatment,
- any new medication prescribed with start and stop dates,
- substitute equipments (crutches, plaster...) if prescribed,
- any other information such as sick leaves and home helps (nurse, home cleaner...).

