## **7. STUDY OBJECTIVES AND PURPOSE**

The purpose of this study is to compare the efficacy and the safety profile of benfluorex and pioglitazone in type 2 diabetic patients, not optimally controlled on sulfonylurea, over 1 year.

The primary objective will be to demonstrate the non-inferiority of the combination sulfonylurea plus benfluorex compared to the combination sulfonylurea plus pioglitazone on the evolution of HbA1c.

Both benfluorex and pioglitazone will be administered at optimal dosage for the treatment of type 2 diabetic patients insufficiently controlled on sulfonylurea monotherapy.

The main secondary objective is to demonstrate the superiority of benfluorex combined with sulfonylurea compared to pioglitazone combined with sulfonylurea on LDL cholesterol level.

The other secondary objectives will be to evaluate and compare over 1 year both combination therapies on the following:

- Fasting Plasma Glucose evolution.
- Insulin Resistance assessed by homeostatic model assessment (HOMA-IR).
- Cardiovascular risk profile.
- Safety and acceptability.
- Cost of the two treatments through an economic balance.

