**Other:**

- **Economic outcomes:** use of a patient diary to record information regarding any adverse event and any medical, para-medical visit or complementary examination apart from the protocol occurring during the study.
- **Serum library** to perform further tests in diabetes (no genetic test), its complication markers and safety issues in case of necessity.

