### 9.6. Participant withdrawal criteria

#### 9.6.1. Withdrawal criteria

Premature discontinuation of treatment, does not necessarily mean that the patient prematurely stops the participation in the study. Information to be collected during the follow-up of these participants is given in section 9.6.2. These follow-up modalities are used to insure the efficacy and safety evaluation of all patients who received the study drug.

The reasons for premature discontinuation of treatment are:

- **Adverse events or any condition incompatible with continuation of either treatment** according to the judgement of the investigator or for which the continuation of the study is recommended (refer to the investigator's brochure of benfluorex and pioglitazone monography in appendices 5 and 6). These include:
  - **Hypoglycaemia incompatible with treatment continuation**, e.g. occurrence of one episode of severe hypoglycaemia or repeated non severe hypoglycaemia (> 3 per month) if the sulfonylurea dose can not be decreased anymore.
  - **ALAT increase > 3 times the ULN value**, after 2 consecutive tests performed in 7 days apart (see appendix 5).
  - **Cardiac failure** (see appendix 10).
  - **Clinically significant anaemia** defined by an haemoglobin level < 12g/dL in men and < 11g/dL in women and a decrease  $\geq 1.5$  g/dL in men and  $\geq 1$  g/dL in women (see appendix 12).

- **Major deviation to protocol incompatible with continuation of either treatment** (including pregnancy).
- **Treatment failure (lack of efficacy) defined as uncontrolled metabolic state with:**
  - **HbA1c > 9.5% at W16 or HbA1c > 9% at W28 or W40** unless increase to dose level B is still possible. If external factors (poor compliance, change of diet and lifestyle, occurrence of infectious or inflammatory disease, intake of corticosteroids) are detected, the investigator will reinforce diet advice and recommendations about treatment intake and/or study protocol compliance. At the following study visit, if the HbA1c is still > 9% the study treatment will be stopped.
  - **or hyperglycaemia** unexplained by external factors and confirmed by either:
    - o clinical symptoms (thirst, polyuria,...) and FPG  $\geq$  13.9 mmol/L
    - o or no symptom and FPG  $\geq$  13.9 mmol/L at 2 consecutive measurements separated by an interval of 2 to 4 weeks.
- **Any medical event requiring administration of an unauthorised concomitant treatment** (see paragraph 10.3).

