### 9.6.2. Procedure

The investigator must record the reason(s) and the exact date of premature discontinuation of treatment in the case report form.

If more than one reason is given, the investigator must indicate the main reason.

The following data must be collected and recorded in the CRF during the withdrawal visit with a priority order (1 to 5):

- Main evaluation criterion: **HbA1c** sampling for the last value under treatment should be performed **before** stopping the study treatment and if not possible as soon as possible within 10 days after stopping the study treatment.
- **Fasting plasma glucose, serum insulin and lipids** (LDL cholesterol, HDL cholesterol, total cholesterol, triglycerides): sampling should be performed **before** stopping the study treatment to be considered as the last value under treatment and if not possible, as soon as possible after stopping the study treatment.

- **Full physical examination** (including sitting blood pressure, heart rate, body weight, waist circumference), **ECG 12-lead, echocardiography** and **full biology** at the time of premature discontinuation.
- **Adverse events** (including hypoglycaemic episodes), concomitant medications and compliance to the study treatment.
- **Economic outcomes.**

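### Section 13.1 ties the CRF resource-use page to adverse events, while section 8.1 counts any contact outside the protocol, so contacts not reported as adverse events may be missed

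*Protocol*

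**What the plan says.** The objective is in protocol section 7: "Cost of the two treatments through an economic balance".

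Section 8.1, under the heading for other criteria, defines the economic outcome by its source: "use of a patient diary to record information regarding any adverse event and any medical, para-medical visit or complementary examination apart from the protocol". The second half of that scope does not depend on an adverse event.

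Section 13.1 gives the recording rule for the later pharmacoeconomic comparison: "the investigator will report on a specific page of the CRF in case of adverse events the additional information". The list that follows covers visits beyond the study visits, hospital stays, examinations the protocol does not require, transport, treatment changes, new medication, equipment, sick leave and home help.

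Two other places mention economic data without an adverse-event condition. Section 9.6.2 introduces its list with "The following data must be collected and recorded in the CRF during the withdrawal visit with a priority order (1 to 5", and economic outcomes are the last item. The investigation schedule, Figure (8.2.2) 1, marks the economic balance at selection and at end of study. Neither place says what is to be recorded.

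**The concern.** The diary and the CRF page have different scopes, and the CRF page is the narrower. Read literally, section 13.1 turns a comparison of treatment costs into something closer to a comparison of the costs of adverse events.

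This matters more in this trial than in many. The arms are compared on glycaemic control, and poor control is an obvious reason for extra visits and tests that nobody need report as an adverse event. If the arms differ in how often that happens, the omission differs too. It is also a fault of data collection: a statistical analysis plan cannot recover contacts that never reached the database.

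**Working it through.** The protocol states no figure on this point, so there is nothing to reproduce. The check sets the sections side by side and follows a contact from the patient to the database.

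**1. Scope.**

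| Type of contact | Section 8.1 (diary) | Section 13.1 (CRF page) |
|---|---|---|
| Visit or test for a reported adverse event, e.g. oedema | counted | counted |
| Visit or test outside the protocol, no adverse event reported | counted | trigger not met |
| New medication, any reason | not named | listed under the adverse-event trigger, but also on the concomitant-treatment pages of the CRF (section 10.3) |

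The gap is the second row, with any transport and sick leave that go with such a contact.

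**2. Route to the database.** Section 10.5 makes the diary a source document kept in the patient's medical file. Under section 18.1 it is the CRF original that goes to the sponsor for data management. Section 18.2 adds electronic transfers from the central laboratory, the IVRS and echocardiography; the diary is not among them. A second-row contact therefore has no stated path beyond the medical file.

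**3. Does the adverse-event definition close the gap?** In part. Section 12.3.1.1.1 includes "any worsening during the study of a symptom or a disease already present when the participant entered the study", any symptom, and abnormal test findings "deemed clinically relevant by the investigator". Thirst, polyuria or clearly worsening diabetes can qualify. But section 12.2 keeps a laboratory abnormality out of the adverse-event section if it is a pre-existing condition that has not got worse. Consider a patient who enters with HbA1c 8.5% (section 9.3 admits values above 7% and up to 10%) and is still at 8.5% at W28, without symptoms and with FPG under 13.9 mmol/L. Nothing has worsened. The patient is below the 9% treatment-failure limit that section 9.6.1 sets for W28, so treatment continues. Extra GP visits or glucose tests for this patient fall within section 8.1, but section 13.1 is not triggered unless the investigator chooses to report an adverse event.

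**4. What the omission does to the comparison.** For arm k, let a_k be contacts per patient linked to a reported adverse event and n_k the other contacts outside the protocol. Section 8.1 counts T_k = a_k + n_k; the section 13.1 page alone counts R_k = a_k. Then

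R_1 − R_2 = (T_1 − T_2) − (n_1 − n_2).

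If n_1 = n_2, the difference in contacts is right and only the totals are too low. If they differ, the error has the size of that difference, and its sign depends on which arm has more such contacts.

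The documents give neither a_k nor n_k, so the following values are assumptions that show the mechanism only. With r = n/a, the share recorded is 1/(1 + r): 80% for r = 0.25, 67% for r = 0.5 and 50% for r = 1.0. With a = 1.0 in both arms and n = 0.5 against 0.8, the totals are 1.5 and 1.8, a difference of 0.3, while the page shows 1.0 and 1.0, a difference of 0. These figures ignore anything picked up at withdrawal or end of study, so they are the worst case for the assumed rates.

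**The case against.** The strongest reply is that section 13.1 is not the only route. Section 9.6.2 requires economic outcomes in the CRF at every withdrawal visit, whatever the reason, and section 9.6.1 names as one reason "Treatment failure (lack of efficacy) defined as uncontrolled metabolic state with". The schedule adds collection at selection and end of study. Section 18.1 says the CRF is built to hold everything the protocol requires, and the diary is checked at visits, so the information exists at source.

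Much of this stands, and it rules out three stronger readings.

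- A reader might infer that resource use reaches the CRF solely through adverse events. It does not: the withdrawal visit and the schedule carry no such condition, so a patient who stops for lack of efficacy cannot be said to contribute nothing. Medication is recorded whatever its cause.
- A reader might infer that contacts caused by poor control are costed at zero. The protocol has no costing or missing-data rule, and symptomatic or worsening hyperglycaemia can itself be an adverse event.
- A reader might infer that the balance favours the less effective arm. That is plausible, but it needs contact rates the documents do not give.

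The reply does not close the gap. The withdrawal visit helps only patients who stop treatment. The entries at withdrawal, selection and end of study have no content of their own: either they take over the list in section 13.1 with its adverse-event trigger, or they are undefined. A general statement that the CRF holds all required data does not settle which of two scopes is required.

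**Conclusion.** The point holds as a conflict of scope between sections 8.1 and 13.1 on a stated secondary objective. Extra visits and examinations, with their transport and sick leave, may be missed when they are not linked to a reported adverse event and the patient stays on treatment. The loss may be unequal between arms. Its size and direction cannot be derived from the protocol.

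The conclusion assumes that the CRF page follows section 13.1 as written and that the undefined economic entries elsewhere do not ask about such contacts. If the CRF, which is not shown, already records every diary contact, the defect is one of wording. Conclusions on HbA1c, LDL cholesterol and safety do not depend on it. It is worth correcting because it is cheap to correct during data collection and hard to repair afterwards.

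**What to change.** 1. In section 13.1, replace the adverse-event trigger with wording such as: for every adverse event, and for every medical or paramedical contact or additional examination not required by the protocol, whether or not an adverse event was reported, as entered in the diary under section 8.1.
2. Add one yes/no item to the CRF page: was this contact linked to a reported adverse event? Adverse-event costs can then still be shown separately.
3. State in section 9.6.2 and in the schedule that the economic entries at withdrawal, selection and end of study use this same content.

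The cost is one sentence, one CRF item and two cross-references, plus slightly more data entry at sites. The diary is already meant to hold these contacts and is already checked at each visit from W0, so no new patient burden is needed. No dose, schedule or clinical rule changes.
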